### Sample size calculation

A power analysis was performed based on a one-sided 97.5% confidence interval for the effect of study arm (intervention or control), an expected 15% primary endpoint rate and a 7.5% non-inferiority margin. To obtain a power of 90%, 960 patients are needed (480 per treatment arm). To account for possible effects of dropout and missing data (10%) we will recruit 1066 patients. This sample size should also yield sufficient power for the analysis of secondary endpoints.

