### Allocation

Computerized block randomization (stratified for center) will take place within 24 h after surgery through ALEA, a web-based application managed by the Clinical Trial Center (CTC) of the Erasmus MC. Random blocks of different lengths are used. Eligible patients will be randomized in a 1:1 ratio to arm A (short course) or arm B (standard course). Each patient will be given a unique study number. An independent data manager from the CTC who is not involved with the clinical practice or patient recruiting created the randomization sequence. The result of the randomization and the patient study number will immediately be provided through ALEA per email to all parties predefined in the system who should receive such notifications.

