### Statistical analysis

We anticipate a 15% rate of infectious complications and mortality in this study population. A 7.5% difference (non-inferiority margin) in the primary endpoint rate is deemed acceptable between the intervention group and control group. This margin is considered acceptable since mortality is expected to account for a negligible proportion within the primary endpoint and infectious complications after appendectomy can be well treated with minimum morbidity and long-term consequences.

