A nationwide prospective cohort study from the Netherlands in 2014 showed that in most patients (78%) antibiotics were given for 5 days or more after surgery for complex appendicitis. The authors concluded that 3 days of antibiotics led to a similar rate of infectious complications. Surgical site infections and intra-abdominal abscesses were seen in 1.3% and 1.6% (*p* = 0.89) and 8.0% and 8.9% of patients (*p* = 0.81), respectively [30]. In Denmark, postoperative prophylaxis of 3 days has become standard care already [58]. Moreover, in several hospitals in the UK 24 h (three doses) of antibiotics has been introduced.

Two limitations of this study should be mentioned. Firstly, the present study is non-blinded. Blinding for treatment allocation would require patients in arm A (48 h) to remain admitted to the hospital and receive a placebo drug intravenously for 3 days. This would put a significant strain on length of hospital stay and costs for the participating hospitals. More importantly, in terms of good clinical decision-making it is important for the treating physician to know whether or not the patient is still receiving actual antibiotics. It is important to reduce risk of bias wherever possible, yet blinding in this trial would not be feasible or desirable. Another limitation is the diagnosis of complex appendicitis which can be rather subjective and dependent on individual surgeons’ opinions [59]. As we strived for this trial to follow clinical practice, we chose to keep the definition of complex appendicitis simple (*a gangrenous and/or perforated appendicitis or appendicitis in presence of intra-abdominal abscess*) and to rely on the surgeon’s intraoperative judgement. For quality assurance, a static image or video of the appendicitis is taken for patients included in the APPIC trial. This way, we will be able to assess the reliability and reproducibility of the diagnosis afterwards.

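### The blanket statement that the sample size also gives sufficient power for the secondary endpoints does not hold for SSI or mortality, and holds for IAA only for a large increase

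*Protocol article*

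**What the plan says.** The protocol article's Sample size calculation section addresses one test only: "A power analysis was performed based on a one-sided 97.5% confidence interval for the effect of study arm", with "an expected 15% primary endpoint rate and a 7.5% non-inferiority margin". From this it concludes: "To obtain a power of 90%, 960 patients are needed (480 per treatment arm"), and "To account for possible effects of dropout and missing data (10%) we will recruit 1066 patients". The next and last sentence of that section reads: "This sample size should also yield sufficient power for the analysis of secondary endpoints".

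The section on secondary outcome measures opens its list with IAA, SSI and mortality as separate rates. It continues with antibiotic duration, length of stay, reoperation, percutaneous drainage, readmission, costs and others. The Secondary endpoints part of the statistical analysis compares all of them by adjusted linear or logistic regression at a two-sided 0.05 level and sets no non-inferiority margin for any.

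On how often the components occur, the document says two things. The Discussion, describing a Dutch cohort that compared 3 days of antibiotics with longer courses, reports "Surgical site infections and intra-abdominal abscesses were seen in 1.3% and 1.6"% and 8.0% and 8.9% respectively. The Statistical analysis section says that "mortality is expected to account for a negligible proportion within the primary endpoint".

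**The concern.** The sentence presents adequate power as a property of the design for the secondary endpoints without distinction. A sample sized for a 15% composite and a 7.5-point margin does not carry over to an endpoint that occurs in 1–2% of patients, still less to one described as negligible.

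The composite pools IAA, SSI and death, so readers will look at the separate rates to see where any difference lies. With the sentence in the published protocol, a non-significant SSI or mortality comparison can be cited as an adequately powered finding of no harm, in support of dropping the longer course. For those endpoints the trial could not bear that reading.

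**Working it through.** **Inputs.** 480 evaluable per arm, or 533 if all 1066 are evaluable (Sample size calculation); 1:1 allocation (Allocation); two-sided 0.05 (Secondary endpoints); SSI 1.3% and 1.6%, IAA 8.0% and 8.9% (Discussion, cited cohort). No mortality rate is given, so 0.1% to 0.5% is assumed. Covariate adjustment is ignored.

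**1. The plan's own figure.** Non-inferiority, 15% in both arms, margin 7.5 points, one-sided 0.025, 90% power:

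n per arm = (1.960 + 1.282)² × 2 × 0.15 × 0.85 / 0.075² = 476.4, so 477 per arm and 954 in total, against 960 stated. Power at 480 per arm is 90.2%. Inflation: 960 / 0.90 = 1066.7, against 1066. The primary calculation reproduces.

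**2. Binary secondary endpoints.** Power = Φ[(d − 1.960 × SE0) / SE1], where d is the difference, SE0 = √(2p̄(1−p̄)/n) with p̄ the mean of the two rates, and SE1 = √((p1(1−p1) + p2(1−p2))/n).

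- SSI 1.3% to 2.6%, n = 480: p̄ = 0.0195, SE0 = 0.00893, SE1 = 0.00892. (0.0130 − 0.0175)/0.00892 = −0.504, so power is 31%. The expected counts are about 6 against 12 events (480 × 0.013 and 480 × 0.026).
- IAA 8.0% to 12.0%, n = 480: p̄ = 0.10, SE0 = 0.0194, SE1 = 0.0193. (0.0400 − 0.0379)/0.0193 = 0.106, so power is 54%.

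| Comparison | 480 per arm | 533 per arm |
|---|---|---|
| SSI 1.3% to 2.6% (doubling) | 31% | 34% |
| SSI 1.6% to 3.2% (doubling) | 37% | 40% |
| SSI 1.3% to 3.9% (threefold) | 72% | 76% |
| IAA 8.0% to 12.0% (×1.5) | 54% | 59% |
| IAA 8.0% to 15.5% (+7.5 points) | 95% | 97% |
| IAA 8.0% to 16.0% (doubling) | 97% | 98% |
| Mortality 0.1% to 0.5% (assumed) | 20% | 22% |
| Mortality 0.5% to 1.0% (assumed) | 14% | 16% |

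The normal approximation flatters the rare endpoints. By simulation with Fisher's exact test at 480 per arm, power is 24% for SSI 1.3% to 2.6% and 2% for mortality 0.1% to 0.5%.

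**3. Smallest increase with 80% power, 480 per arm** (same formula, solved for the higher rate):

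- SSI: 1.3% to 4.3% (ratio 3.3); 1.6% to 4.8% (ratio 3.0).
- IAA: 8.0% to 13.6% (ratio 1.70); 8.9% to 14.7% (ratio 1.66).
- Mortality (assumed baselines): 0.1% to 1.9% (ratio 19); 0.5% to 2.8% (ratio 5.6).

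With 533 per arm the SSI figures fall only to 4.1% and 4.6%, and the IAA figures to 13.3% and 14.4%.

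**4. Continuous endpoints.** Detectable standardized difference = (1.960 + z) × √(2/480), which is 0.18 for 80% power and 0.21 for 90%. With assumed standard deviations, a 1-day difference in length of stay has 97% power at SD 4, 87% at SD 5 and 73% at SD 6. The planned 3-day difference in antibiotic duration has over 99% at any SD up to 10 days.

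**5. If the cohort rates are too low for this trial.** Its IAA and SSI rates sum to 9.3% (8.0 + 1.3) and 10.5% (8.9 + 1.6), below the planned 15%. Scaling both up to 15% puts SSI at 1.3 × 15/9.3 = 2.1% or 1.6 × 15/10.5 = 2.3%. Even at an assumed 3%, a doubling to 6% has only 61% power.

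**The case against.** The strongest reply is that power is defined only against a target difference, and the plan names none for the secondary endpoints, so the sentence cannot be shown to be simply untrue. This stands, and so do several related points. The secondary aims named under Trial objective and hypothesis are length of stay and cost-effectiveness; for length of stay, as for antibiotic duration, the sample is ample for modest differences. IAA is well powered for a doubling. The cohort rates are background, not planning inputs. The article condenses a full protocol that may hold further calculations, so the absence of a calculation is not itself the point. Any change in practice is tied to the primary composite, not to a secondary test.

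A reader might therefore infer too much in three ways:

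- That the sentence is wrong for every secondary endpoint. The figures for continuous outcomes and for a doubling of IAA contradict that.
- That power is only 6–7%, taking the cohort's own contrasts (SSI 1.3% v 1.6%, IAA 8.0% v 8.9%) as the target. Those are near-null differences that nobody proposed to detect.
- That reoperation and percutaneous drainage are underpowered. The document gives no rate for either, so this cannot be said.

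What does not stand is the use of the missing target as a defence for SSI and mortality. At the cited SSI rates no increase below about threefold reaches 80% power. A 7.5-point rise in SSI is detectable with over 99% power, but it means going from 1.3% to 8.8%, nearly sevenfold.

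**Conclusion.** The concern holds in a limited form. As an unrestricted statement the sentence cannot be sustained. It fails for SSI, where a doubling has 31–37% power and about a threefold rise is needed for 80%. It fails for mortality under any baseline consistent with the plan's own description of it as negligible. It holds for IAA only for an increase of about 1.7-fold or more, and for continuous endpoints from a standardized difference of about 0.2.

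These figures rest on 480 evaluable per arm, two-sided 0.05, unadjusted comparisons, background-cohort rates for SSI and IAA, and an assumed mortality of 0.1–0.5%. Having all 1066 patients evaluable, or an SSI rate of 3%, does not change the conclusion for SSI. The primary sample size is correct and is not affected. This is a misstated property of the design, to be put right in the text.

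**What to change.** Keep the sentence but restrict it to the endpoints for which it holds: continuous endpoints (standardized difference of about 0.2), and IAA with its detectable difference stated (80% power for a rise from 8.0–8.9% to 13.6–14.7%, with the source of the baseline given).

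Then add, in substance: the trial is not powered for SSI, mortality or other rare events; these will be reported as estimates with 95% confidence intervals alongside the planned regression; and a non-significant difference in them will not be taken as evidence of no difference. Reoperation and percutaneous drainage need no separate label unless an expected rate is supplied.

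The cost is a text change. No extra patients are needed, and the primary analysis and the planned secondary models stay as they are. The stated property becomes less favourable for the rare endpoints.

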### Recruitment

Recruitment of participants started on 12 April 2017 and is ongoing. Additional participating hospitals may be recruited to ensure feasibility of the trial. The target of 1066 patients is expected to be completed in early 2020.

### Allocation

Computerized block randomization (stratified for center) will take place within 24 h after surgery through ALEA, a web-based application managed by the Clinical Trial Center (CTC) of the Erasmus MC. Random blocks of different lengths are used. Eligible patients will be randomized in a 1:1 ratio to arm A (short course) or arm B (standard course). Each patient will be given a unique study number. An independent data manager from the CTC who is not involved with the clinical practice or patient recruiting created the randomization sequence. The result of the randomization and the patient study number will immediately be provided through ALEA per email to all parties predefined in the system who should receive such notifications.

### Implementation

Before the start of the trial, each center is visited by the research team to inform and instruct the involved personnel on study-specific procedures. Surgeons and residents are trained how to assess the type of appendicitis to decide whether patients are eligible for study participation by means of recorded examples of all types of appendicitis.

### Blinding

Blinding for treatment allocation in this study would not only be difficult to achieve, but is also undesirable because good clinical decision-making during the postoperative course requires specific knowledge of antibiotics that have or have not been given to the patient. Therefore, this is an non-blinded trial.

### Data collection and management

A data manager from each participating hospital will carry out the data collection in collaboration with the trial coordinator. Baseline demographics, as well as preoperative, intraoperative and postoperative variables, will be collected from the electronic medical records. The validated iMTA-PCQ will be used for cost analysis. A list of all variables is provided in the full study protocol. All data will be entered into the secure online ALEA database, a system validated and supported by the Erasmus University Medical Centre. Data will be handled confidentially and anonymously. A short intraoperative video or static picture(s) should be recorded for quality assurance of the diagnosis complex appendicitis. Quality control will involve collecting data on adherence to the intervention, patient inclusion and follow-up, as well as monitoring the quality of the data entry. Qualified data managers of the CTC of the Erasmus MC will perform quality control and assurance. Checks and queries will be performed to ensure quality, consistency, and completeness. Missing data and inconsistencies will be reported back to the centers to be clarified by the local responsible investigator.

### Statistical analysis

We anticipate a 15% rate of infectious complications and mortality in this study population. A 7.5% difference (non-inferiority margin) in the primary endpoint rate is deemed acceptable between the intervention group and control group. This margin is considered acceptable since mortality is expected to account for a negligible proportion within the primary endpoint and infectious complications after appendectomy can be well treated with minimum morbidity and long-term consequences.

#### Primary endpoint

The study hypothesis will be tested by a one-sided 97.5% confidence interval for the effect of study group (absolute risk difference). This confidence interval will be adjusted for effects of type of appendicitis and age (as a single categorical covariate: < 16 years old/non-perforated, < 16 years old/perforated, ≥16 years old/non-perforated, ≥16 years old/perforated) using the method proposed by Klingenberg [41, 42]. Non-inferiority will be established if the upper limit of the confidence interval is lower than 7.5%. Both per-protocol and intention-to-treat analyses will be performed. In a secondary analysis, logistic regression analysis will be performed to identify predictors of the composite primary endpoint. Independent variables in this model will include treatment group and also age, sex, surgical approach, type of appendicitis, ASA score, and center, as well as significant interaction effects of these independent variables with treatment group.

#### Secondary endpoints

General patient characteristics and other clinically relevant parameters will be compared between the intervention group and the control group with the independent samples Student’s *t* test or the Mann-Whitney test in case of continuous outcome variables and the chi-square or Fisher’s exact test in case of categorical outcome variables where appropriate. All secondary endpoints will be compared between the trial arms using linear regression for continuous outcomes and logistic regression for dichotomous outcomes, with adjustment for age, sex, surgical approach (open versus laparoscopic), type of appendicitis, ASA score, and center. In case of non-normally distributed continuous outcomes, appropriate transformation of these outcomes will be applied. A two-sided significance level of 0.05 will be used for all secondary analyses. Uncertainty with respect to cost-effectiveness will be analyzed by bootstrapping results for incremental costs and health effects. The results will be shown in an acceptability curve that indicates the probability that the intervention meets several cost-effectiveness thresholds.

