### Trial setting

The trial will run in at least 14 hospitals in the Netherlands. This includes one academic hospital and 13 teaching hospitals. The participating hospitals are listed on the trial webpage (www.appictrial.nl). In all participating hospitals appendectomy is mostly performed laparoscopically.

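### The fully adjusted logistic model fixed for every dichotomous secondary endpoint is not usable for mortality, and is unstable for surgical site infection if its rate is near 1.5%

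*Protocol article*

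**What the plan says.** The Secondary outcome measures section of the protocol article lists IAA, SSI and mortality as separate secondary endpoints, next to other dichotomous ones such as reoperation and readmission. The Secondary endpoints section under Statistical analysis then says: "All secondary endpoints will be compared between the trial arms using linear regression for continuous outcomes and logistic regression for dichotomous outcomes". The adjustment set is center, ASA score, age, sex, type of appendicitis and open or laparoscopic approach, tested two-sided at 0.05. The one fallback concerns continuous outcomes: "In case of non-normally distributed continuous outcomes, appropriate transformation of these outcomes will be applied". Fisher's exact test is mentioned, but for patient characteristics and other clinical parameters; the sentence after it sends the secondary endpoints to regression.

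Three other places bear on how this works out:

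- Trial setting: "The trial will run in at least 14 hospitals in the Netherlands". The Recruitment section allows more to join.
- Statistical analysis, opening paragraph: mortality is expected to be a negligible part of the composite.
- Discussion, on the Dutch cohort: "Surgical site infections and intra-abdominal abscesses were seen in 1.3% and 1.6" percent for SSI, then 8.0% and 8.9% for IAA.

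The Primary endpoint section adds a secondary logistic model for predictors of the composite. It contains treatment and the same six covariates, "as well as significant interaction effects of these independent variables with treatment group".

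**The concern.** The rule covers all dichotomous secondary endpoints, whatever their event count. A maximum-likelihood logistic model with a coefficient for each center needs events in both arms, and preferably in most centers. If one arm has no event, the treatment odds ratio is zero or infinite. If a center has no event, its coefficient diverges and its patients add nothing to the treatment comparison.

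Mortality is part of the primary composite, and the Data monitoring and safety section makes it a special focus. SSI is one of the two infectious components. A reader of the trial report will look at these separate rates to see what drives the composite, so the prescribed comparison should be one that can be computed and read.

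The predictor model raises a smaller, separate matter. Keeping those treatment interactions that reach significance, out of six candidates, invites chance findings.

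**Working it through.** **1. The plan's own figure.** The Sample size calculation section gives "A power analysis was performed based on a one-sided 97.5% confidence interval for the effect of study arm", "an expected 15% primary endpoint rate and a 7.5% non-inferiority margin" and "To obtain a power of 90%, 960 patients are needed (480 per treatment arm"). Check: n per arm = (1.960 + 1.282)² × 2 × 0.15 × 0.85 / 0.075² ≈ 477, or 954 in total. Power at 480 per arm is 90.2%. For dropout, 960 / 0.9 = 1066.7 against the stated 1066. The sample size is reproduced and is not at issue.

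**2. Coefficients.** Treatment 1, age 1, sex 1, approach 1, type 1 to 2, ASA 1 to 2, and center 14 − 1 = 13 give 19 to 21 plus the intercept. Assumption: center enters as fixed terms.

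**3. Events = N × rate.** The range per coefficient runs from (960 patients, 21 coefficients) to (1066 patients, 19 coefficients). The article gives no mortality figure, so 0.1% to 0.5% is an assumed range.

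| Endpoint and rate | Events in 960 | Events in 1066 | Events per coefficient |
|---|---|---|---|
| Mortality 0.1% (assumed) | 1.0 | 1.1 | 0.05–0.06 |
| Mortality 0.2% (assumed) | 1.9 | 2.1 | 0.09–0.11 |
| Mortality 0.5% (assumed) | 4.8 | 5.3 | 0.23–0.28 |
| SSI 1.3% (Discussion) | 12.5 | 13.9 | 0.59–0.73 |
| SSI 1.6% (Discussion) | 15.4 | 17.1 | 0.73–0.90 |
| SSI 5% (assumed) | 48.0 | 53.3 | 2.3–2.8 |
| IAA 8.0% (Discussion) | 76.8 | 85.3 | 3.7–4.5 |
| IAA 8.9% (Discussion) | 85.4 | 94.9 | 4.1–5.0 |

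**4. Mortality: chance that at least one arm has no death.** With 1066 / 2 = 533 per arm and equal risk p, let q = (1 − p)^533. The chance is 1 − (1 − q)².

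- p = 0.1%: q = 0.587, chance 83%.
- p = 0.2%: q = 0.344, chance 57%.
- p = 0.5%: q = 0.069, chance 13%.

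Put another way, if d deaths occur, all fall in one arm with probability 2 × 0.5^d: 50% for two deaths, 25% for three.

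**5. SSI: centers with no event.** With 14 equal-sized centers of 1066 / 14 = 76 patients, the expected number is 14 × (1 − p)^76.1. This is 5.2 at 1.3% and 4.1 at 1.6%. At 5% it is 0.3.

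**6. SSI and IAA: simulation of the prescribed model (1066 patients, 14 centers).**

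- At SSI 1.45%, some coefficient diverged in 99.8% of trials, but the treatment coefficient did so in only 0.2%.
- With a true odds ratio of 2 and about 1.5% SSI overall, the mean adjusted log odds ratio was 0.767 against a true 0.693, about 11% too large. A treatment-only fit gave 0.736, so part of this comes from rarity alone.
- At SSI 5%, some coefficient diverged in 30% of trials, the treatment term in none, and the type I error was about 5%.
- At IAA 8.5%, some coefficient diverged in 2% of trials and the type I error was about 5%.

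**7. Interactions.** Six covariates give six candidate interactions with treatment. If each is one independent test at 5%, the chance of keeping at least one false one is 1 − 0.95⁶ = 26%.

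**The case against.** The strongest reply is that a journal article condenses the full protocol, and that sparse-data methods and the handling of center belong in the document not shown. This stands in part. The text does not say whether center is fixed or random. A random center term would cut the count to 6 to 8 coefficients and raise SSI to between 12.5 / 8 = 1.6 and 17.1 / 6 = 2.9 events per coefficient. But the article does not leave the model open: it assigns one to all secondary endpoints. An arm without a death also has no finite odds ratio, however center is handled.

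A second reply is that the SSI rate is taken from a background cohort, whereas the trial plans on a 15% composite. With IAA near 8.5% and negligible mortality, that leaves about 15 − 8.5 = 6.5% for SSI, or 0.065 × 960 = 62 events and about 3 per coefficient. This stands, so the SSI point is conditional on a rate near 1.5%.

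A reader might also infer more than the documents support:

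- *That the SSI test rejects too often.* Simulations at 1.45% gave 5.2% to about 7% for the likelihood-ratio test and 1.7% to 4.8% for the Wald test. One set of only 400 trials gave 9%, which larger sets did not reproduce. The article names neither test.
- *That the IAA comparison is unstable.* With 77 to 95 events, it keeps an error rate of about 5% to 6%.
- *That linear regression with transformation fails for visit counts and the Comprehensive Complication Index.* No monotone transformation removes a mass at zero, but the article gives no distribution for either, and a routine outpatient visit is planned for everyone. With assumed zero shares of 60% to 91%, a simple comparison of means still had a type I error of 4.5% to 6.0%.
- *That a transformed length of stay, or odds ratios that cannot be set against the 7.5-point margin, are errors.* The first is a choice of estimand. The margin applies to the composite only, and no component margin exists.

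**Conclusion.** The point holds for rare dichotomous secondary endpoints. It is firm for mortality: under an assumed 0.1% to 0.5%, the prescribed odds ratio is not estimable in roughly 83% to 13% of trials because an arm has no death, and 1 to 5 deaths cannot support some 20 coefficients in any case. For SSI it is conditional. At the Discussion's rates the model has under one event per coefficient and is unstable, mainly in its center terms; the treatment term usually survives and its type I error is not clearly inflated. At about 5% or more little remains. These sizes assume fixed center terms, 14 equal-sized centers and 960 to 1066 analyzed patients; more hospitals would make matters somewhat worse.

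The interaction rule is a lesser fault in an analysis already labelled secondary. The 26% assumes independent tests.

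**What to change.** In the analysis plan, before database lock:

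- For mortality, and for any other dichotomous secondary endpoint with too few events for the full model (SSI if near 1.5%), replace the fully adjusted logistic regression with an exact or Firth-penalized comparison containing treatment and at most the age-by-perforation strata. State in advance how too few is judged, and apply it to the event count pooled over arms.
- For the components of the composite, report risk differences with 95% confidence intervals, using the stratified method already named for the primary endpoint, where events allow.
- In the predictor model, do not retain interactions on significance alone. Pre-specify a short list, or label all of them exploratory.

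The models for continuous outcomes need no change on this account. The cost is wording only. The drawback is that the rare-event comparisons adjust for fewer covariates and leave out center, which is the randomization stratifier.
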